## Abstract

**Introduction:**

People with type 2 diabetes (T2D) can improve glycaemic control or even achieve remission through weight loss and reduce their use of medication and risk of cardiovascular disease. The Glucose Lowering through Weight management (GLoW) trial will evaluate whether a tailored diabetes education and behavioural weight management programme (DEW) is more effective and cost-effective than a diabetes education (DE) programme in helping people with overweight or obesity and a recent diagnosis of T2D to lower their blood glucose, lose weight and improve other markers of cardiovascular risk.

**Methods and analysis:**

This study is a pragmatic, randomised, single-blind, parallel group, two-arm, superiority trial. We will recruit 576 adults with body mass index>25 kg/m^2^ and diagnosis of T2D in the past 3 years and randomise them to a tailored DEW or a DE programme. Participants will attend measurement appointments at a local general practitioner practice or research centre at baseline, 6 and 12 months. The primary outcome is 12-month change in glycated haemoglobin. The effect of the intervention on the primary outcome will be estimated and tested using a linear regression model (analysis of covariance) including randomisation group and adjusted for baseline value of the outcome and the randomisation stratifiers. Participants will be included in the group to which they were randomised, under the intention-to-treat principle. Secondary outcomes include 6-month and 12-month changes in body weight, body fat percentage, systolic and diastolic blood pressure and lipid profile; probability of achieving good glycaemic control; probability of achieving remission from diabetes; probability of losing 5% and 10% body weight and modelled cardiovascular risk (UKPDS). An intention-to-treat within-trial cost-effectiveness analysis will be conducted from NHS and societal perspectives using participant-level data. Qualitative interviews will be conducted with participants to understand why and how the programme achieved its results and how participants manage their weight after the programme ends.

**Ethics and dissemination:**

Ethical approval was received from East of Scotland Research Ethics Service on 15 May 2018 (18/ES/0048). This protocol (V.3) was approved on 19 June 2019. Findings will be published in peer-reviewed scientific journals and communicated to other stakeholders as appropriate.

**Trial registration number:**

ISRCTN18399564.

Strengths and limitations of this studyThis trial will provide robust evidence of the clinical and cost-effectiveness of a scalable tailored diabetes education and behavioural weight management programme versus diabetes education alone in adults with a recent diagnosis of type 2 diabetes.If shown to be cost-effective, the intervention being evaluated could be readily integrated into existing UK care pathways and delivered to large numbers of people.The behavioural programme is already widely available across many countries and this model of care could be readily adopted across healthcare services internationally.This trial only includes follow-up at 6 and 12 months and longer term data may be needed to understand the longer term impact of these programmes.Consent has been obtained to follow-up participants through national registries and medical records for up to 15 years.

## Background

The treatment of diabetes and related complications (eg, cardiovascular disease, amputation, kidney failure) uses approximately 10% of the UK NHS budget.^1^ This is predicted to rise to 17% in 2035 as the number of people with diabetes in the UK rises to 6.25 million, of which 5.6 million cases will be adults with type 2 diabetes (T2D).^1^ Adults who are living with T2D are at increased risk of developing physical and mental health comorbidities and have reduced quality of life and shorter life expectancy.^2 3^ There are considerable social and economic costs to the individual living with diabetes as well as to wider society.^1 2 4^

While T2D is typically characterised as a progressive, irreversible condition, there is evidence of remission in patients losing weight through bariatric surgery^5 6^ or closely supervised very-low-calorie formula diets.^7 8^ However, many patients with T2D may be unsuitable for or unwilling to undergo these interventions and, given their high cost and reliance on specialists, they are unlikely to be widely adopted in the NHS in the near future. Partial or complete remission of T2D has also been observed following smaller weight losses achieved through behavioural interventions.^9^ Moreover, even without remission, weight loss and behaviour change can lead to improvements in health outcomes in people who have diabetes. We have shown that losing a moderate amount of weight or making healthy behaviour changes (eg, increasing physical activity, reducing alcohol, energy and fat intake) in the first year after diagnosis can reduce the likelihood of stroke or heart attack in the next 5–10 years^10–12^ and increase the likelihood of achieving remission at 5 years.^13^

The Look AHEAD trial demonstrated that intensive specialist-led behavioural programmes could lead to weight loss and reductions in cardiovascular risk factors over 8-year follow-up.^14^ However, there are currently insufficient resources in the UK NHS to provide intensive, specialist-led behavioural programmes to 3.2 million individuals who have T2D and the additional 200 000 individuals who are diagnosed each year. Instead, current guidelines focus on structured diabetes education (DE) and dietary advice,^15^ which is cheaper and scalable but has small, short-term effects on weight and glycaemia, and relatively poor uptake.^16–18^ A recent systematic review found that supportive behaviour change programmes (with ≥11 hours of contact time) achieve greater reductions in weight and glycated haemoglobin (HbA_1c_) than structured education without additional support (≤10 hours).^17^ Integrating effective but scalable behaviour change programmes into care pathways for T2D could potentially improve patients’ glycaemic control and related risk factors and reduce complications. This would improve health and quality of life for people living with diabetes and reduce the burden of diabetes on healthcare resources.

We have previously shown that commercial open-group behavioural weight management programmes, such as WW (formerly Weight Watchers) or Slimming World, offer a scalable and cost-effective way to help people lose weight and reduce risk of diabetes.^19–22^ A randomised trial in the USA showed that a combination of WW classes and remote dietary counselling achieved greater weight losses and reductions in HbA_1c_ than standard care over 1 year in people with diabetes.^23^ A quarter of participants randomised to this programme achieved good glycaemic control (HbA_1c_ below 53 mmol/mol) at 12 months compared with 14% of those receiving standard care. In the UK, a similar intervention has been developed for use in the NHS that combines referral to WW with NICE-compliant DE and dietary advice. However, this programme is unlikely to be widely commissioned without robust evidence of cost-effectiveness. The proposed trial will provide reliable evidence on the relative effectiveness and cost-effectiveness of a tailored diabetes education and behavioural weight management programme (DEW) versus DE, for people with a recent diagnosis of T2D (≤3 years).

## Objectives

### Primary objective

To evaluate the effect of tailored DEW versus DE on HbA_1c_ at 12 months in adults with a recent diagnosis of T2D.

### Secondary objectives

To evaluate the effect of DEW versus DE on:

body weight, body fat percentage, blood pressure, lipid profile and modelled 10-year cardiovascular risk at 6 and 12 monthsprobability of achieving clinically significant weight loss, good glycaemic control or diabetes remission at 6 and 12 monthschanges in diet and physical activity at 6 and 12 monthspsychosocial factors associated with successful weight control at 6 and 12 months.

To evaluate the within-trial cost-effectiveness of DEW vs DE.

To assess the extent to which the two programmes reach the target population.

To explore participant and practitioner experiences of the two programmes and the extent to which these programmes meet their needs.

To clarify causal mechanisms and identify contextual factors associated with variations in outcome.

To identify barriers and facilitators to maintenance of weight management behaviours after treatment cessation.

## Methods and analysis

### Trial design

This is a pragmatic, randomised, single-blind, parallel group, two-arm, superiority trial. Participants will be randomised to either the tailored DEW or to DE. Block randomisation will be used with a 1:1 allocation stratified by sex and duration of diabetes (figure 1).

**Figure 1 F1:**
[figure not shown]
Participant flow diagram.

### Study setting

Research active primary care practices which currently refer patients with T2D (≤3 years duration) to local structured DE (Diabetes and Education Self-Monitoring for Ongoing and Newly Diagnosed (DESMOND)) and have active WW groups in the local community.

### Participants

Participants will be 576 adults with overweight or obesity who have a diagnosis of T2D in the past 3 years.

#### Inclusion criteria

Body mass index≥25 kg/m^2^.Age≥18 years.Diagnosis of T2D within the previous 36 months (confirmatory blood test will not be required).Capable of giving informed consent.Have a good understanding of the English language (study materials are not tailored to support non-English language speakers).Willing to be randomised.Willing to attend follow-up visits at a local participating general practitioner (GP) practice or research centre.

#### Exclusion criteria

Using insulin.Previous/planned bariatric surgery.Current/planned pregnancy.Current diagnosis of eating disorder.Already received a structured DE programme.GP considers unsuitable.Participation in another structured behaviour change programme for diet and/or physical activity within the past 3 months.

## Interventions

### ​Tailored Diabetes Education and Weight management

The tailored DEW programme was developed and is delivered by WW. It lasts 6 months and is overseen by a registered dietitian with experience in diabetes, diet and behaviour counselling and specific training in the standard WW programme.

#### ​Structured DE

The structured DE programme is delivered remotely (video conferencing/telephone) on a 1:1 basis by the registered dietitian over two education sessions, 3–5 weeks apart (total time 1 hour 30 min, divided between two calls). It covers a standardised QISMET-accredited core curriculum but can then be adapted for the individual’s needs. Additional self-help education materials to support the curriculum will be available online and are delivered to all participants via email or mail at the patient’s preference. These materials may be minimally tailored to the individual participant. Information on the materials can be found at www.weightwatchers.com/uk/live-well-diabetes. During the education sessions, materials on goal setting, understanding diabetes, the glycaemic index, carbohydrates, physical activity and weight management are reviewed.

#### ​Behavioural programme

The behavioural weight management component consists of free membership of WW for 6 months. This includes attendance at weekly in-person group meetings (30–40 min) held at a variety of times in a range of local community venues. These are open-group meetings (new people may join or leave the group at any time) and are led by a coach (trained lay person with experience of the programme). Meetings include a confidential weigh in with the coach and a 30 min interactive education session led by the coach which includes advice on diet, physical activity and positive mindset, using behavioural strategies (eg, goal setting, self-monitoring, problem solving, modifying the personal food environment and relapse prevention). Peer support is available from coaches and other group members. Participants can be accompanied by a friend, relative or carer. Participants will also have access to the WW app, online digital tools and standard materials such as recipe booklets, physical activity guidance and meal trackers for the duration of the intervention. Participants can contact their coach for support/advice between meetings via an online chat function.

#### ​Participant engagement

Once a referral is received, the registered dietitian will telephone the participants, welcome them to the programme, sign them up to a local WW meeting and arrange the first education session. Participants are also given an information sheet with details of how to contact the dietitian directly. A closed social media support group will be formed and all participants will be encouraged to join if they wish to do so. Activity on the group forum will be monitored and supported by the registered dietitian. Each week, the dietitian will contact 2–5 participants (selected at random from those who have participated in the programme for longer than 3 months) via the social media group or phone. Participants can also contact the dietitian proactively during the intervention period for additional remote support where needed, but they will be encouraged to do so via the social media group in the first instance. If participants miss four or more WW standard in-person meetings, their local coach will call to help the individual return to the programme.

### ​Diabetes education

We will recruit from Clinical Commissioning Groups (CCGs) where the commissioned standard care DE is the DESMOND programme.^16 18^ This is a structured DE programme for people with a recent diagnosis of T2D (≤3 years since diagnosis). Participants can attend 6 hours of structured self-management group education, covering: thoughts and feelings about diabetes; understanding diabetes and glucose—what happens in the body; understanding risk factors and complications associated with diabetes; understanding monitoring and medication; how to take control—food choices and physical activity and planning for the future. The structured education is delivered in 1 day or 2 half days by two trained healthcare professionals in local healthcare or community venues. Sessions are delivered in groups of up to 10 participants, and participants can bring a friend or partner with them. The education sessions are supported by specially developed resources.

### Outcomes

#### ​Primary outcome

The 12-month change from baseline in HbA_1c_.

#### ​Secondary outcomes

The 6-month change from baseline in HbA_1c_.

The 6-month and 12-month changes from baseline in body weight, body fat percentage, systolic and diastolic blood pressure, total cholesterol, high-density lipoprotein cholesterol and low-density lipoprotein cholesterol.

Good glycaemic control (HbA_1c_ <53 mmol/mol) at 6 and 12 months.

Remission from diabetes (HbA_1c_ <48 mmol/mol and without glucose-lowering medication for ≥2 months) at 6 and 12 months.

Weight loss ≥5% and ≥10% of initial body weight at 6 and 12 months.

Modelled cardiovascular risk (UKPDS) at 12 months.

#### Behavioural and psychosocial outcomes

The 6-month and 12-month changes from baseline in objectively measured physical activity (accelerometry), self-reported physical activity, objective marker of fruit and vegetable intake (plasma carotenoids) and self-reported dietary intake.

The 6-month and 12-month changes from baseline, adjusted for baseline, in dietary restraint, control over food cravings, emotional eating, self-regulatory skills, social support and diabetes-related quality of life.

#### Health economic outcomes

Detailed micro-costing of DEW and DE.

Health and social care resource use over 12 months (medical notes, registry data, resource use questionnaire).

Self-reported out-of-pocket costs and lost productivity (eg, due to days off work, up to 12 months).

The 12-month quality-adjusted life years (QALYs) based on Health-Related Quality of Life (HRQoL) (EQ-5D-5L)^24 25^ and capability/well-being (ICECAP-A).^26 27^

Total and incremental costs from NHS and societal perspectives; incremental net (monetary) benefit; incremental cost-effectiveness and cost-utility ratios; value of information estimates.

#### ​Uptake and adherence

Number and characteristics of participants who:

are offered the opportunity to participate in the trial.enrol in the trialattend the intervention.adhere to the intervention (including specific intervention components).

A detailed protocol for process evaluation will also be developed.

### Visits and measurements

#### ​Visit schedule

Participants will be asked to attend measurement appointments at a participating primary care practice or research centre at 0, 6 and 12 months. Details of measures at each assessment are summarised in figure 2. Participants will be reimbursed for reasonable travel expenses and given an honorarium for attending measurement appointments (£10 for baseline and 6-month visits, £30 for the 12-month visit). Honoraria for assessment attendance are not dependent on intervention attendance/completion.

**Figure 2 F2:**
[figure not shown]
Schedule of enrolment, interventions and assessments.

#### ​Anthropometric measures

Anthropometric measurements will be made at participating primary care practices or research centres by research-trained healthcare professionals (hereafter ‘research nurses’) blind to intervention allocation, in line with standardised operating procedures. Participants will be asked to remove shoes and heavy clothing items. Height will be measured in centimetres using a mounted stadiometer (make and model dependent on practice). Where possible, weight (kg) and body fat percentage will be measured using a calibrated Tanita segmental body composition analyser (Tanita Ltd; MA Tokyo, Japan; model dependent on practice) which will be provided to practices by the research team. Where we have an insufficient number of Tanita scales to measure body fat at a practice, we will measure weight (kg) only using calibrated electronic scales (model dependent on practice). To maximise the number of participants for whom we can measure body fat, we will prioritise the use of Tanitas at large practices with a large number of eligible patients, and Clinical
Research Networks (CRN)-led practices (as CRN nurses can transport the Tanita scales to numerous practices). Blood pressure will be measured three times in a resting state using a calibrated OMRON automatic blood pressure monitor (OMRON Healthcare UK, Milton Keynes, UK; model dependent on practice).

If a research nurse is not available to conduct follow-up assessments, assessments may be conducted by trained research centre staff. If participants are unable to attend follow-up appointments at a participating practice, the research team may offer appointments at the local hospital or research centre, or home visits. Participants who are unable or unwilling to attend a visit will be asked to provide a self-measured weight. All other participants will also be asked for a self-measured weight at the time of appointment booking to enable us to quantify the degree of misreporting of self-measured weights.

#### ​Biochemical measures

Participants will be asked to provide a blood sample for the measurement of HbA_1c_, lipid profile and carotenoids. If possible, this sample will be taken at the practice at the same time as the anthropometric measurements. Blood samples will be collected in three tubes labelled with an anonymised barcode (4.9 mL serum tube for lipid profile, 2.6 mL Ethylenediaminetetraacetic acid (EDTA) tube for HbA_1c_, 4.9 mL and lithium heparin (LH) tube for carotenoids). The LH tube is light sensitive, so it will be wrapped in foil to avoid degradation. Samples will be placed in a Royal Mail Safebox and posted via first-class mail to the central laboratory for analysis. Each sample is stable for up to 3 days at room temperature. Plasma samples for analysis of carotenoids will be frozen and analysed in batches.

#### ​Behavioural measures

##### Physical activity

Physical activity will be measured objectively using a triaxial accelerometer (Axivity AX3, Newcastle, UK) which measures raw acceleration (m/s^2^). Participants will be asked to wear the accelerometer on their non-dominant wrist continuously for seven consecutive days and nights. The device is small, light and waterproof and is worn like a watch. It does not need to be taken off while showering, bathing or swimming.

At the baseline visit, the nurse will take the participant through the accelerometer instruction sheet. They will demonstrate to the participant how they should wear the monitor on their wrist. The nurse will also ensure that the timing of the monitor and return is feasible for the participant. The study team will initialise the accelerometer and will post it out to the participant with the instruction sheet. The participant will wear the monitor for 7 days and nights and will complete an activity log. For the 6-month and 12-month visits, accelerometers will be mailed out to participants. At the end of 7 days, the participant will be asked to post the device back to the research centre using prepaid, preaddressed materials. Trained staff will download the data from the accelerometer and check it to ensure the integrity of the data recording. This method has been used in large-scale epidemiological studies including the UK Biobank study in 100 000 individuals.^28^ Data will be analysed using established methods used in UK Biobank. The outcome variables of interest are vector magnitude, a measure of total physical activity and intensity distribution, from which duration of time in different levels of physical activity can be inferred.

Self-reported physical activity will be measured using the Recent Physical Activity Questionnaire, a validated measure of four domains of physical activity (leisure time, occupation, commuting and domestic life) that has been used in a number of intervention studies and large-scale epidemiological studies.^29 30^ This will be administered as part of the self-report questionnaires.

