#### ​Enrolment

Patients willing to participate will be asked to contact the research centre for more information. This can be by telephone, email or reply slip. Research centre staff will answer any questions and conduct a telephone screening. If patients are eligible and willing to participate, the research staff will check that they have received the participant information sheet (sending another if they have not) and arrange a baseline assessment with the research nurse at a local participating practice or research centre.

At the baseline visit, the research nurse will take informed consent. This will include ensuring that participants have read the information sheet and had the opportunity to ask questions. They will also confirm eligibility, including an objective measure of height and weight, before taking the rest of the baseline measurements. At the end of each day, the research nurse will email the study coordinator a list of participants who have formally enrolled on the trial.

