#### ​Method of implementing the allocation sequence

When participant eligibility has been confirmed at the baseline visit, the practice will inform the study coordinator. The study coordinator will enter the participant’s details into the trial database which will automatically assign an intervention to the participant.

The study coordinator (or member of their team) will write to the participant to inform them of their intervention allocation and will also inform the participant’s GP. The study coordinator or the GP (depending on practice and intervention allocation) will also send a referral form to the intervention provider, giving the details of the participant who has been referred to them.

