#### ​Statistical analysis plan

A detailed statistical analysis plan will be developed and signed off by the Trial Steering Committee (TSC) prior to analysis. Participants will be analysed in the group to which they were randomised, based on the intention-to-treat principle. The intervention effect, representing the baseline-adjusted difference in change from baseline to 12 months in HbA_1c_ between the intervention and control group, will be estimated using a linear regression model including randomisation group, baseline value of HbA_1c_ (ie, analysis of covariance (ANCOVA)) and the randomisation stratifiers (sex, duration of diabetes). The missing indicator method^34^ will be used to ensure inclusion of participants with a missing baseline value of HbA_1c_. Participants with missing values of HbA_1c_ at 12 months will be excluded (ie, a complete-case analysis). If there are >5% of participants with missing values of HbA_1c_ at 12 months, a sensitivity analysis will be performed using multiple imputation by chained equations; full details of this analysis will be provided in the statistical analysis plan.

Continuous secondary outcomes will be analysed using the method described earlier. Binary secondary outcomes will be analysed using a logistic regression model including randomisation group and the randomisation stratifiers.

For the primary outcome, effect modification by (1) sex, (2) index of multiple deprivation (high, low), (3) educational qualification (below postsecondary, postsecondary and above postsecondary) and (4) duration of diabetes (<1 year; 1–3 years) will be tested using an F-test of the relevant multiplicative interaction parameter in the ANCOVA model. If the p value for a particular interaction is <0.05, then the intervention effect and 95% CI will be estimated within the relevant subgroups.

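### As written, the 7-day baseline accelerometer week normally follows randomisation and may follow the participant learning the arm, so accelerometry change may rest on a baseline that allocation has affected

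*Protocol article*

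**What the plan says.** **Measurement.** The Protocol article (Physical activity) limits what happens in person: "At the baseline visit, the nurse will take the participant through the accelerometer instruction sheet". The nurse also demonstrates how the device is worn and checks that the timing suits the participant. The device itself comes later: "The study team will initialise the accelerometer and will post it out to the participant with the instruction sheet". Then: "The participant will wear the monitor for 7 days and nights and will complete an activity log".

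**Allocation.** Under Method of implementing the allocation sequence: "When participant eligibility has been confirmed at the baseline visit, the practice will inform the study coordinator". The coordinator then enters the participant's details "into the trial database which will automatically assign an intervention to the participant". A letter tells the participant the arm, and a referral form goes to the provider. Enrolment adds that "At the end of each day, the research nurse will email the study coordinator a list of participants" who have enrolled. Under Participant engagement, the dietitian phones DEW participants once the referral arrives. Under Blinding, participants are not blinded.

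**Use of the value.** Behavioural and psychosocial outcomes lists accelerometry as a change from baseline at 6 and 12 months. Physical activity is also among the Secondary objectives. The Statistical analysis plan section states: "Continuous secondary outcomes will be analysed using the method described earlier". That method is an ANCOVA adjusting for the baseline value.

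**The concern.** A baseline used for adjustment or subtraction should be fixed before allocation can influence it. Here the steps leading to allocation start on the day of the visit, while the monitor still has to be initialised, posted and worn for a week. If participants in one arm change their activity once they know where they are being referred, part of that response is recorded as baseline and removed from, or added to, the estimated effect.

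At stake is the trial's only objective measure of physical activity. The alternative is a questionnaire completed by unblinded participants. An analysis plan written later cannot recover a pre-allocation measurement that was never taken, so this is a matter for the protocol.

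**Working it through.** **1. What is not touched.** The sample size concerns HbA1c and reproduces from the Sample size calculation section (SD 16 mmol/mol, correlation 0.8, difference 3 mmol/mol, 90% power, 25% attrition; 5% significance taken as two-sided):

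- Residual SD = 16 × √(1 − 0.8²) = 9.6.
- n per arm = 2 × (1.960 + 1.282)² × 9.6² / 3² ≈ 215.2, rounded up to 216 (power 90.1%).
- 216 / 0.75 = 288 per arm, 576 in total, as stated.

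HbA1c comes from a blood draw, taken with the visit measurements where possible, and not from the posted device. Neither the primary outcome nor N depends on this point.

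**2. Order of events, side by side.**

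| Step | Accelerometry | Allocation |
|---|---|---|
| At the visit | Explanation and demonstration only | Eligibility confirmed |
| Same day | – | Nurse emails the list of enrolled participants |
| Afterwards, undated | Device initialised and posted | Database entry assigns the arm; letter and referral sent |
| After the device arrives | 7 days and nights of wear | – |

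No sentence makes database entry, letter or referral conditional on the wear week or the return of the device. Followed as written, wear normally comes after assignment. Whether it also comes after the letter depends on dates that the document does not give.

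**3. Size of the possible bias.** The document gives no inputs for accelerometry, so these are assumptions:

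- τ: true between-arm effect at follow-up.
- b: within-arm slope of follow-up on baseline.
- f: share of τ already present as a between-arm difference in the baseline wear week.

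Let Z be the arm and x the activity unaffected by allocation. Follow-up is y = b·x + τ·Z + error, and the recorded baseline is x* = x + f·τ·Z. Substituting x = x* − f·τ·Z gives y = b·x* + τ(1 − b·f)·Z + error. ANCOVA therefore estimates τ(1 − b·f). The raw change score estimates τ − f·τ = τ(1 − f).

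Share of the true effect retained:

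| | f = 0 | f = 0.1 | f = 0.25 | f = 0.5 |
|---|---|---|---|---|
| ANCOVA, b = 0.4 | 100% | 96% | 90% | 80% |
| ANCOVA, b = 0.6 | 100% | 94% | 85% | 70% |
| ANCOVA, b = 0.8 | 100% | 92% | 80% | 60% |
| Raw change | 100% | 90% | 75% | 50% |

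A simulation (400,000 participants, true effect 0.3 SD) agreed with the ANCOVA formula to within about 0.012. If the DE arm reacts more in that week, f is negative and the effect is overstated: f = −0.1 with b = 0.6 gives 1 + 0.06 = 106%.

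**4. Precision cost of dropping the baseline.** With equal variances and baseline–follow-up correlation r, the standard error rises by a factor of 1/√(1 − r²): 1/√0.84 = 1.09 at r = 0.4, 1/√0.64 = 1.25 at r = 0.6, and 1/√0.36 = 1.67 at r = 0.8.

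**The case against.** The strongest reply is that the order is inferred. No sentence dates database entry, the letter or the referral. The same-day email lists enrolled participants and is not called a randomisation trigger. The nurse does discuss the timing of the monitor. Figures 1 and 2 could not be consulted, and the article condenses a fuller protocol, so an unstated hold on allocation cannot be excluded. This stands as a limit on certainty. It does not remove the point, because the text as published contains no hold and a week of wear after posting is long compared with a same-day notification.

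Three further objections also stand in part:

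- **Knowledge of the arm is what matters.** A database assignment cannot change activity; only the letter or provider contact can. A reader might infer that every participant wears the baseline device already knowing the arm. The document does not show that.
- **The ANCOVA is not expressly tied to accelerometry.** Accelerometry is listed apart from the section headed Secondary outcomes, and in its own list only the psychosocial item mentions adjustment for baseline. The link runs through the Secondary objectives. The change from baseline uses the same value in any case.
- **Size and direction are assumed.** Values such as f = 0.5 need half of the 6- or 12-month effect to appear in one week, around a welcome call that only then arranges the first education session. A reader might also infer bias towards no difference. DE covers physical activity too, so the sign is open.

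**Conclusion.** The point holds as a fault of sequence. As written, the baseline wear week normally falls after randomisation and may fall after the participant knows the arm, and accelerometry change would be measured from that week. This rests on reading the enrolment, allocation and accelerometry sections together, and on there being no hold on allocation stated elsewhere.

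It does not follow that the accelerometry result is biased. Bias needs a between-arm difference in that week. With none, nothing is lost. For b between 0.4 and 0.8, a small early difference (f = 0.1) leaves 92–96% of the effect under ANCOVA and a large one (f = 0.5) leaves 60–80%; a negative f overstates it. The document cannot say which applies. One behavioural outcome is exposed; HbA1c and the 576 stand. The change is worth making because it is cheap.

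**What to change.** **Participants still to be recruited** (recruitment was expected to run to August 2020). State that the allocation letter and provider referral, or database entry itself, wait until the 7-day baseline wear has ended, with a short cap so that an unworn or unreturned device cannot stall entry to the trial. The cost is about 1–2 weeks between baseline measures and referral, with some risk of losing interest in a trial that has already needed extra recruitment strategies. No extra patients or staff are needed. If such a hold already operates, one sentence saying so settles the point.

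**Participants already randomised.** Compare device timestamps with allocation-letter dates. Do not treat wear after the letter as a true baseline. Report a between-arm comparison of 6- and 12-month accelerometry that neither adjusts for nor subtracts post-letter wear, at least as a sensitivity analysis. The cost is a date check and some loss of precision, which becomes substantial if activity is strongly correlated over time and most baselines prove to be post-letter. Also state explicitly whether the baseline-adjusted ANCOVA applies to accelerometry.
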